##### Data Analysis Plan

###### Analysis of Alcohol Use Outcomes

Descriptive statistics for breathalyzer reading data will be summarized overall, by group (SAM only, SAM+TRAC, and SAM+TRAC-ER) and across time periods (T1-T4). The primary outcome is the number of drinking days in the past month, which is defined as the days on which individuals did not report 2 negative breathalyzer results. The rate of drinking (incidence of drinking) is the number of drinking days observed within the past month. The secondary outcomes include the number of drinks per drinking day, the number of days with binge drinking episodes, and the number of days for which HIV risk behaviors occur. All these outcomes are count data. The goal of this analysis is 2-fold: first, short-term analysis at the end of the 2-month intervention period, and, second, long-term analysis at the end of 9 months. We will fit a generalized linear model [50], with a general formulation for count data as follows:

g(E(y_i_)) = g(μ_i_) = x'_i_β (1)

where *y_i_* is the outcome variable for (*i*=1,2,3,...,*n*), *n* is the total number of observations, *μ*_i_=*E*(*y_i_*) is the expected count, *g* is the link function (a mathematical function connecting the counts with the explanatory variables), *β* is a vector of regression parameters to be estimated, and *x_i_* is a vector of independent covariates to be included in the model. These covariates include group, time, age (or age group), gender identity, sexual orientation, and site.

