Every morning during the SAM periods, participants will receive a push notification asking them to report the number of drinks consumed in the previous day (if applicable), time spent drinking, alcohol withdrawal symptoms, and sexual risk behaviors. The app will also send requests for breathalyzer readings at least 2 times per day in response to visits to risky locations and through random requests. At the time of providing the breathalyzer reading, participants will also complete a brief mobile survey using the study app that includes questions related to their alcohol use. Participants can view a log of their breathalyzer readings in the app. Participants will have the option to report a trigger in the app and provide details about the trigger, including the location where the trigger was generated. Participants who are randomized to the TRAC-ER intervention will receive a harm reduction message based on the type of trigger (social, emotional, or other) they report. A guided breathing exercise and urge surfing exercise are included in the app for those in the TRAC and TRAC-ER conditions. Figure 1 presents a screenshot of the app. If, at any point during the monitoring periods, the app stops collecting GPS data, the study team will reach out to determine whether the participant accidentally turned off location tracking, lost their mobile phone, or is experiencing other technical difficulties.

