**31-90**				
	Morning survey: sent between 7 AM and 10 AM (based on participant preference)	✓	✓	✓
	Random breathalyzer reading and breathalyzer request survey: request at a random time between 11 AM and 5 PM and at a random time between 5 PM and 11 PM	✓	✓	✓
	Location survey and breathalyzer reading: request breathalyzer request survey and breathalyzer reading when participant leaves a risky location	✓	✓	✓

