###### Baseline and Follow-Up Measures

An assessment battery will be administered to all participants at T1, T2, T3, and T4. This will include several measures of alcohol use as well as more exploratory variables, including alcohol cravings, alcohol consequences, the use of alcohol treatment services, HIV risk behaviors, and experiences of discrimination related to participants’ identity as sexual and gender minority individuals. Table 2 presents a description of the key study measures.

**Table 2 table2:** Description of key study measures.

Construct and time		Measure	End point	Description
Drinking days, 2× daily		Breath alcohol content	Primary	BACtrack Mobile breathalyzer result sent via mobile app; measured 2× daily for 8 weeks during the intervention and for 1 month before T1^a^, T3^b^, and T4^c^; 2 negative readings per day=nondrinking day
Drinks per drinking day, daily		Self-reported alcohol use through app	Secondary	3 items: alcohol consumed (yes or no), number of drinks, and time spent drinking; measured daily during the intervention and for 1 month before T1, T3, and T4
Binge drinking episodes, daily		Self-reported alcohol use through app	Secondary	Occasions when participants had ≥5 drinks based on self-reported number of drinks; measured daily during the intervention and for 1 month before T1, T3, and T4
Alcohol withdrawal symptoms, daily		Single-item AWSC^d^ [40]	Exploratory	1 item: alcohol withdrawal symptom severity on a scale of 0 to 9; those scoring ≥2 are asked to complete the 17-item AWSC, which assesses the severity of symptoms; measured daily during intervention and for 1 month before T1, T3, and T4
Sexual activity, daily		Self-reported through app	Exploratory	6 items: past-day sexual activity, number of partners, partner type, partner HIV status, type of sexual activity, condomless sex, and PrEP^e^ use
Location characteristics, up to 2× daily		Self-reported through app	Exploratory	12 items assessing alcohol and substance use, sexual behaviors, peer use of alcohol or substances, and harassment or discrimination experienced
Alcohol use, T1, T2^f^, T3, and T4		PROMIS^g^ Short Form–Alcohol Use 7a [41]	Exploratory	7 items that assess general alcohol use and problem drinking in the past 30 days (eg, drank too much and drank heavily)

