###### Methods to Decrease Attrition and Missing Data

During the first 3 months of the study, participants will receive daily reminders to complete SAM, which will include information about potential incentives. Individuals in the SAM+TRAC and SAM+TRAC-ER arms will have weekly contact with research staff during the TRAC sessions and will receive reminders about upcoming appointments. We will contact participants 1 month before their follow-up monitoring periods to remind them about upcoming tasks and to ensure that contact information is up to date. The use of a novel smartphone app and a mobile breathalyzer, which has been highly rated by participants in past studies, will also help to ensure continued engagement with, and enthusiasm for, the study.

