###### Short-Term Outcome Analyses

After 3 months, we will fit the aforementioned model to the data and compare the groups at T1 and T2 while adjusting for the covariates. The PROC GENMOD procedure in SAS (SAS Institute Inc) will be implemented to estimate the parameters of the model, where we specify a log-link function, Poisson distribution for the count data, an offset (which is a function of the total exposure), and the covariates. We will address overdispersion using negative binomial distribution. Overdispersion occurs when the expected count for the outcome variable is not the same as its variance. The generalized estimating equation procedure will be used to account for correlation induced by the repeated observations at T2.

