###### Long-Term Outcome Analyses

At 9 months, the time variable will include observations at T1 to T4, and the procedure implemented for the short-term analysis will be repeated with the inclusion of additional covariates in the form of interaction terms among the groups and follow-up times (T1-T4). The interaction effect is central to the comparison of the groups over the study period. Generalized estimating equation fit criteria and quasi-likelihood under the independence model criterion value will be used to determine the adequacy of model fit. This modeling framework facilitates the easy computation of hypothesis tests and CIs for effects, which will form the basis of our inferential strategy in this project. Specifically, contrast statements will be used to test specific subgroup comparisons. Multiple imputation procedure will be implemented whenever necessary for missing data points. SAS (version 9.4 or higher) will be used for all analyses, and a standard 5% significance level will be used for all statistical tests.

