Our study has promising strengths, but it must be considered in light of several limitations. While the use of ecological momentary assessment (EMA) provides advantageous opportunities for real-time trigger location data and convenience reporting through smartphones, prior EMA studies highlight the potential exhaustion that participants may experience, which may reduce the level of participation. This study may further explore convenient assessment windows to diminish the intensity of EMA sampling. In addition, as previously mentioned, SMMT communities experience unique sociostructural challenges, such as unemployment, homelessness, forced displacement, and community violence [59]. These systems of power may operate dynamically and render difficulties in participating fully and equitably in hazardous alcohol use prevention programs [60]. Finally, the real-time tracking of alcohol use behaviors of participants may give rise to reporting bias. In the context of alcohol-related stigma, social desirability biases may subject participants to aligning their responses to the expectations of societal norms around alcohol consumption; however, the use of breathalyzers will help to protect against self-report bias.

Prior studies have also reported concerns for temporal bias, where participants were reluctant to complete location- and time-based–triggered EMA surveys due to the inconvenient times at which the surveys were sent. Similarly, EMA studies related to substance use have mentioned challenges with the time frame for EMA sampling [61]. In this study, EMA assessments will occur between 11 AM and 11 PM to avoid disturbing participants. However, participants in prior studies have discussed that these hours may not be representative of the time frames when drinking occurs because alcohol use may occur later at night, along with variations in mood and social activities. Thus, we may explore the potential options for personalized hours of EMA sampling for participants. Breathalyzer device loss may also pose a challenge. However, unlike prior EMA studies that distributed mobile phones and experienced challenges with device loss [62], our study enables participants to use their existing smartphones to use the app, which will reduce instances of device loss or misplacement.

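### The primary outcome scores a missed breath reading as drinking: this dilutes any true effect and, if compliance changes differently by arm, can create or hide a difference

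*Protocol article*

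**What the plan says.** The section Analysis of Alcohol Use Outcomes makes the primary outcome the past-month count of drinking days, "which is defined as the days on which individuals did not report 2 negative breathalyzer results". Table 2 states the complement: "2 negative readings per day=nondrinking day". Neither has a third category for days with incomplete data.

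Table 1 schedules two random requests on every monitored day: "request at a random time between 11 AM and 5 PM and at a random time between 5 PM and 11 PM". A further request follows each departure from a risky location, and the app description accordingly says: "The app will also send requests for breathalyzer readings at least 2 times per day".

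Two other rules bear on the outcome. Short-Term Outcome Analyses specifies "an offset (which is a function of the total exposure"), without saying which days count as exposure. Long-Term Outcome Analyses says: "Multiple imputation procedure will be implemented whenever necessary for missing data points". Neither says whether a missed breath reading is a missing data point.

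**The concern.** Under the stated rule, one negative reading plus one missed reading has the same value as a positive reading. The endpoint is then a mixture of drinking and non-response. The plan also gives two answers for a missed reading: the definition assigns it a value, while the imputation sentence expects missing data to be filled.

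Missed readings are foreseeable. The Discussion names "potential exhaustion that participants may experience, which may reduce the level of participation". Some drivers of compliance also differ by arm once the intervention starts. In the section on attrition and missing data, the SAM+TRAC and SAM+TRAC-ER "arms will have weekly contact with research staff during the TRAC sessions", and Sessions 2 to 4 review the week's drinking data. If this contact raises compliance, fewer days are scored as drinking without any change in drinking. If app burden lowers compliance in an active arm, a real benefit could be hidden.

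The literal rule can also err the other way. With an extra location-triggered reading, a day with two negatives and one positive would count as nondrinking.

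**Working it through.** **The plan's own figure.** 324 / (1 − 0.20) = 405, so the enrolment target reproduces. It shows that the 20% dropouts are treated as lost from the final sample. The documents give no compliance rate and no mean number of drinking days, so the size of the problem has to be illustrated.

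**Inputs.** From the documents: a 30-day monitoring period and two random requests per day (Table 1). Assumed: D = 10 true drinking days, all scored as drinking; per-reading compliance c; misses unrelated to drinking.

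**Formula.** Let m be the probability that a dry day lacks two readings. Scored days = D + (30 − D) × m.
- Misses fully clustered by day (both readings given or neither): m = 1 − c.
- Independent misses: m = 1 − c².

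**Scored days with D = 10.**

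| c | Clustered | Independent |
|---|---|---|
| 0.90 | 12.0 | 13.8 |
| 0.85 | 13.0 | 15.55 |
| 0.80 | 14.0 | 17.2 |
| 0.75 | 15.0 | 18.75 |
| 0.70 | 16.0 | 20.2 |

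For example, at c = 0.80: 10 + 20 × 0.20 = 14.0, and 10 + 20 × 0.36 = 17.2.

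**Spurious gap with no true effect.**
- 0.80 vs 0.85, clustered: 14.0 − 13.0 = 1.0 day; ratio 13.0/14.0 = 0.93.
- 0.80 vs 0.85, independent: 17.2 − 15.55 = 1.65 days; ratio 15.55/17.2 = 0.90.
- 0.75 vs 0.85: 15.0 − 13.0 = 2.0 days (0.87) clustered; 18.75 − 15.55 = 3.2 days (0.83) independent.

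Varying D from 6 to 12 days at 0.80 vs 0.85, the gap is (30 − D) × 0.05 = 1.2 to 0.9 days clustered, and (30 − D) × (0.7225 − 0.64) = 1.98 to about 1.48 days independent. Exchanging the compliance of the two arms reverses the sign.

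**Dilution with equal compliance.** A true difference is multiplied by 1 − m. At c = 0.80, a true 2-day reduction is scored as 2 × 0.80 = 1.6 days (clustered) or 2 × 0.64 = 1.28 days (independent).

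**Extra location-triggered readings.** If every dry day had three requests, all counting, with independent misses, fewer than two readings would be given with probability (1 − c)³ + 3c(1 − c)².
- c = 0.80: 0.008 + 0.096 = 0.104, so 10 + 20 × 0.104 = 12.08 days.
- c = 0.85: 0.003375 + 0.057375 = 0.06075, so 10 + 20 × 0.06075 = 11.215 days.
- Gap: 0.865 days. Real days would mix two and more requests.

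**Group-by-time comparison.** The long-term analysis rests on the group-by-time interaction with T1 included. If compliance is 0.80 vs 0.85 at baseline and at follow-up, the clustered ratio is 13.0/14.0 both times and the ratio of ratios is 1. The gaps above therefore bias that test only to the extent that the compliance difference arises after baseline.

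**The case against.** The strongest objection is that unequal compliance is assumed, and this has force. Many supports apply to all arms: daily reminders in the first 3 months, weekly completion reports with encouragement for the nonadherent (Process Measures), texts and calls after non-response (Participant Training), and US $1 per timely sample (Ethical Considerations). The extra contact in the active arms is four sessions within a 6-week window, and the scheduled monitoring tasks before T1, T3 and T4 are the same in every arm. Arm bias is thus possible, not shown, and its direction is open. Equal compliance would not remove the problem, though, because the dilution remains.

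The figures depend on how misses cluster and on how many requests count, which is why a range is given.

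Three stronger readings are tempting, and the documents do not support them.
- A reader might infer that dropouts score 30 of 30. The sample size text removes dropouts from the final sample, and imputation may cover unobserved periods.
- A reader might infer that nothing is ever missing. The imputation sentence is not limited to breath readings; it can cover whole periods, covariates and self-reported outcomes.
- A reader might infer that the fitted rate can exceed 1. That needs a particular offset the text does not fix; with 30 calendar days it cannot happen.

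Finally, leaving out days with missed readings is unbiased only if missingness is unrelated to drinking, and people may skip a reading because they are drinking. This is a reason to keep the present rule as a sensitivity analysis, not as the primary definition.

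**Conclusion.** The point holds for monitored days. The definition and Table 2 score a missed reading as drinking, and neither the offset nor the imputation sentence overrides them. That much rests on wording alone. The dilution follows whenever compliance is imperfect: at an assumed 80% per reading, a true difference in days shrinks to between 64% and 80% of its size under two requests per day. A spurious arm difference is conditional on compliance changing differently by arm after baseline. It is most plausible during the intervention months, when the extra contact occurs. A 5-point gap (80% vs 85%) at 10 true days would produce about 1.0 to 1.65 days, and less where location-triggered readings count. All these magnitudes rest on assumed compliance and drinking levels and on misses unrelated to drinking. Because the rule defines the primary endpoint, it should be corrected before outcome data are analysed.

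**What to change.** In Analysis of Alcohol Use Outcomes and in Table 2, define three states for each monitored day:
- drinking, if any reading is positive;
- nondrinking, if at least two readings are given and all are negative;
- unclassified, otherwise.

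Set the offset to log(classified days), or fit a binomial model with classified days as the denominator. State that unclassified days are the missing data points, and impute them with the morning survey and adjacent-day data as auxiliary variables. Self-report then informs the imputation while the endpoint stays breath-based. Report compliance by arm and monitoring period. Keep missing-as-drinking as a sensitivity analysis, read alongside those compliance figures.

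The cost is revised text and some added analysis; no new data are needed, since the morning survey is already collected daily in every monitoring period. The downside is that the primary analysis then assumes missingness is explained by the observed data. The retained sensitivity analysis tests that assumption.

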#### Sample Size Justification

Sample size determination was based on the primary outcome variable: number of drinking days in the past month across the repeated visits corresponding to T1, T2, T3, and T4 for the 3 groups (SAM only, SAM+TRAC, and SAM+TRAC-ER). Data on effect sizes from previous alcohol use interventions [34,35] and our preliminary data (within-participant correlation of 0.69) were used to derive the mean number of days of alcohol use and their SDs. With a final sample size of n=324 (after accounting for a 20% dropout rate with a total n=405), 108 (33%) participants in each group will give us at least 90% power at 5% type I error rate to detect a significant difference among the groups for an effect size of 0.071 when comparing the groups over the study period. This effect size is smaller than a *small* effect as defined by Cohen et al [36].

We expect our sample to have the following characteristics: 48.1% (195/405) cisgender men, 24.9% (101/405) transgender men, 20% (81/405) transgender women, and 6.9% (28/405) nonbinary individuals. Our sample will likely have a higher proportion of transgender participants compared to the general population due to recruitment within health clinics that provide care for transgender patients; we view this as a strength of our study, given the underrepresentation of gender minority individuals in previous alcohol intervention and HIV prevention research.

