#### Description of Study Arms

##### Overview

Participants will be enrolled in the study for 9 months, including the 2-month intervention period and multiple follow-up monitoring periods to assess long-term effects. All participants will begin with a 30-day monitoring period, which will establish baseline alcohol use through daily breathalyzer reading requests and surveys. After this 30-day period, they will complete additional baseline measures (T1) and then begin their assigned intervention, if applicable. After the interventions are delivered, participants will complete an additional self-report (T2). Subsequently, there will be 2 additional monitoring periods and assessments spread across the 9-month study period to assess long-term intervention effects, with some months involving no study activities. A depiction of the participation timeline is included in Figure 2, and details of study activities completed across the study timeline and RCT arms are provided in Table 1.

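### The long-term model takes T1 drinking as a response with a separate mean per arm rather than adjusting for it: valid, but less precise than the data allow

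*Protocol article*

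**What the plan says.** - **Covariates.** Analysis of Alcohol Use Outcomes describes a generalized linear model for counts and states: "These covariates include group, time, age (or age group), gender identity, sexual orientation, and site". Drinking before the intervention is not named.
- **Response and interaction.** Long-Term Outcome Analyses states: "At 9 months, the time variable will include observations at T1 to T4". It adds "interaction terms among the groups and follow-up times (T1-T4", and says: "The interaction effect is central to the comparison of the groups over the study period".
- **Short term.** Short-Term Outcome Analyses will "compare the groups at T1 and T2 while adjusting for the covariates", so T1 is again one of the compared time points.
- **Baseline data.** Description of Study Arms, Overview, has all participants begin with 30 days of monitoring, "which will establish baseline alcohol use through daily breathalyzer reading requests and surveys". The intervention follows T1. Table 1 shows the same activities in all three arms on days 1-30.
- **Conditional adjustment.** Addressing Biological Variables expects stratified randomization to prevent systematic baseline differences. It plans adjustment only for differences that prove statistically significant.
- **Sample size.** Sample Size Justification gives a "within-participant correlation of 0.69" from preliminary data, 108 analysed per arm, an effect size of 0.071 and at least 90% power.

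**The concern.** With group, time and their full interaction over T1 to T4, the model estimates three separate T1 means. The treatment effect at a follow-up visit is then the arm difference at that visit minus the arm difference at T1; on the log scale, a ratio of rate ratios. With complete data the fitted arm-by-visit means are essentially the sample means, so the choice of working correlation does not recover the lost information.

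Randomization implies that the arms share a T1 mean, provided T1 is unaffected by allocation. Subtracting an estimated T1 difference whose expectation is zero adds noise. Conditioning on T1 removes the predictable part of the outcome and adds less. The conditional adjustment does not fill this gap: under randomization a 5% test flags T1 drinking about one time in 20, and the gain comes from the correlation of T1 with outcome, not from imbalance.

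At stake are narrower intervals from data already collected. This matters most for the smallest hypothesized difference, TRAC-ER against TRAC.

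**Working it through.** **Inputs.** From Sample Size Justification: correlation ρ = 0.69, N = 324 analysed (108 per arm), effect size 0.071, alpha 5%, dropout 20%. Assumptions: 0.071 is Cohen's f for the interaction (the metric is not stated), and compound symmetry holds (only one correlation is given).

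**1. The article's own figures.** Recruitment: 324/(1 − 0.20) = 405, as stated. For the repeated-measures interaction test with m visits, λ = f²·N·m/(1 − ρ).
- m = 4: λ = 0.071² × 324 × 4/0.31 = 21.07, df 6 and 963, power 95.1%.
- m = 3: λ = 15.81, power 90.6%; N = 321 gives 90%.

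Both agree with at least 90%. A purely between-group test would give only about 24% with four visits. The sample size therefore fits the interaction test that the article plans.

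**2. Variance for the T2-T4 average** (per arm, in units of σ²):
- Free T1 means (change): (1 + 2ρ)/3 + 1 − 2ρ = 0.793 + 1 − 1.38 = 0.413.
- T1 as covariate: (1 + 2ρ)/3 − ρ² = 0.793 − 0.476 = 0.317.
- Ratio: 0.317/0.413 = 0.7675, so the variance is 23% lower. The standard error ratio is √0.7675 = 0.876, so about 12% smaller.
- Equivalent size: 324 × 0.7675 ≈ 249. That is, 324 analysed as planned inform this contrast about as well as 249 with T1 adjusted.

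**3. A single visit, such as T2:** change 2(1 − ρ) = 0.620; adjusted 1 − ρ² = 0.524; ratio 0.845. The variance is 15.5% lower and the standard error about 8% smaller.

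**4. Sensitivity for the average.** With three follow-ups the ratio simplifies to (1 + 3ρ)/4.

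| ρ | Variance reduction |
|---|---|
| 0.5 | 37.5% |
| 0.6 | 30% |
| 0.69 | 23% |
| 0.8 | 15% |

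If 0.69 is instead the adjacent-visit correlation of a first-order autoregressive pattern, the reduction is 34%.

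**5. Omnibus interaction.** The information lost depends on the shape of the effect: 23% if sustained over T2-T4, 15% if growing linearly, 12% if decaying (1, 0.5, 0.25), 3% if present at T2 only. In the sustained case λ rises from 21.07 to 21.07/0.7675 = 27.5, and power from 95.1% to 98.8%.

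**6. Check on the count scale.** Simulated correlated negative binomial counts (assumed mean 12, variance 49, correlation about 0.69, 108 per arm, 2,000 replicates) were analysed on the log scale both ways, with log(T1 count + 0.5) as the covariate. Both estimators gave a log rate ratio of −0.18. The variance was 22.4% lower for the three-visit average and 14.8% lower for T4 alone.

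**7. Pairwise illustration (an assumption, not a figure from the plan).** Suppose f = 0.071 over four visits, a sustained effect, and equally spaced arms. Then f² = d² × (2/3) × 0.1875 = 0.125d², so adjacent arms differ by d = 0.071/√0.125 = 0.201 SD. The standard errors are √(2 × 0.413/108) = 0.0875 and √(2 × 0.317/108) = 0.0766. Two-sided 5% power is 63% as planned and 75% with adjustment. TRAC-ER against SAM would be 0.402 SD: z = 0.402/0.0875 = 4.59, with power above 99% without adjustment.

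**The case against.** The strongest reply is that nothing here is wrong. T1 in the response with a group-by-time test is a standard longitudinal analysis, unbiased under randomization, and the trial is sized for that test. This stands. A reader might infer bias or overstated power; the documents support neither, since step 1 reproduces the stated power with the planned test.

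Second, the covariate list is introduced by a word that need not be exhaustive, and the analysis plan, which is not shown, may settle the T1 parameterization. This stands only in part. The article itself fixes T1 as a response level, carries the interaction over T1 to T4, and restricts adjustment for baseline differences to significant ones. That is a stated model, not mere silence.

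Third, 23% is close to a favourable case. It is on the variance scale and assumes compound symmetry and an unweighted T2-T4 average, which the article does not name as its contrast. A reader might infer that every comparison loses about a quarter of its precision; steps 3 and 5 show otherwise.

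Fourth, a reader might infer that the pairwise hypotheses as a group lack power. On the assumptions of step 7 that is true of adjacent arms only, and those assumptions are not in the article.

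**Conclusion.** The point holds as a loss of efficiency. The long-term model as described gives each arm a free T1 mean and does not prespecify adjustment for baseline drinking. At ρ = 0.69 under compound symmetry, adjustment would cut the variance by about 23% for the T2-T4 average and about 15% for one visit. The gain for the average is material across correlations from 0.5 to 0.8; the gain in the omnibus test can be as small as 3%. The planned analysis remains valid, and its stated power is not in question. The change is worth making because the baseline value is already collected, but it is an improvement and not the repair of an error.

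**What to change.** Prespecify one of two forms for the primary outcome, and for every count outcome with a T1 value.

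1. **T1 as covariate (the simpler choice).** Responses are T2-T4, or T2 alone for the short-term analysis. Terms are group, visit, group by visit, the listed covariates and the T1 value of the same outcome. Use a form defined at zero, because binge days and HIV-risk days may be zero at T1 and the log of a zero rate does not exist. Either log(T1 count + 0.5) with exposure taken into account, or the untransformed T1 rate, will serve. Keep the planned offset for the follow-up responses.
2. **T1 kept in the response with one mean common to all arms.** This is sound only if randomization follows the 30-day run-in or arms are not disclosed before T1. The article does not state when randomization occurs, so that should be stated first.

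Adjustment should not depend on a significance test of baseline balance. Any pairwise power figure added should be labelled with its assumed effect.

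The cost is one term in the same SAS procedure and a sentence on zeros and exposure. No further data or participants are needed. The choice should be fixed before outcome data are examined by arm.
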